## Abstract

**Background::**

Despite a UK 5-year breast cancer survival rate of 86.6%, patients may develop breast cancer recurrence within the same breast after breast conserving surgery, as well as in the remaining skin or chest wall after mastectomy or in the ipsilateral lymph glands. These recurrences, collectively termed locoregional recurrence (LRR), occur in around 8% of patients within 10 years of their original diagnosis. Currently, there is a lack of robust information on the presentation and prevalence of LRR with no UK-specific clinical guidelines available for the optimal management of this patient group. Additionally, there is a need to identify patterns of LRR presentation and their progression, which will enable prognostic factors to be determined. This will subsequently enable the tailoring of treatment and improve patient outcome.

**Methods::**

The MARECA study is a prospective, multicentre cohort study recruiting patients diagnosed with breast cancer LRR +/- associated distant metastases. Over 50 UK breast units are participating in the study with the aim of recruiting at least 500 patients over a recruitment period of 24 months. The data collected will detail the tumour pathology, imaging results, surgical treatment, radiotherapy and systemic therapy of the primary and recurrent breast cancer. Study follow-up will be for up to 5 years following LRR diagnosis to determine subsequent oncological outcomes and evaluate potential prognostic factors.

**Discussion::**

This study will address the current knowledge gap and identify subgroups of patients who have less successful treatment outcomes. The results will determine the current management of LRR and the prognosis of patients diagnosed with breast cancer LRR +/- distant metastases in the UK, with the aim of establishing best practice and informing future national guidelines. The results will direct future research and inform the design of additional interventional trials and translational studies.

HighlightsBreast cancer locoregional recurrence (LRR), occurs in around 8% of patients within 10 years of their original diagnosis.There is a lack of robust information on the presentation and prevalence of locoregional recurrence with no UK-specific clinical guidelines available for the optimal management of this patient group.The MARECA study will help to determine oncological outcomes and evaluate potential prognostic factors, subsequently enabling the tailoring of treatment, improved patient outcomes and aid the production of national guidelines.

## Background

Breast cancer is diagnosed in ~55 000 women per year in the UK^1^ and 5-year survival for all breast cancer patients is favourable at 86.6% due to advances in systemic treatment and implementation of the NHS breast screening programme^2^. Despite this high survival rate, a proportion of patients are diagnosed with a breast cancer recurrence within the conserved breast, ipsilateral skin or chest wall following mastectomy, or in the ipsilateral axillary, supraclavicular, infraclavicular, or internal mammary lymph nodes. These cancer recurrences are collectively termed locoregional recurrence (LRR).

In-breast local recurrence after breast conserving surgery (BCS) is thought to be due to the growth of previously undetected microscopic tumour foci, which may present when the patient presents with new symptoms or more commonly discovered on follow-up (surveillance) mammography. Local recurrence after mastectomy may present as subcutaneous nodules on the chest wall with dermal lymphatic involvement, which may be associated with worse prognosis^3^. The Early Breast Cancer Trialists’ Collaborative Group (EBCTCG) meta-analyses^4,5^ suggest that patients diagnosed with LRR after BCS and radiotherapy may have a better subsequent prognosis than those patients who initially received mastectomy. However, an adequately powered study is required to examine the prognostic effect of initial breast cancer surgery (BCS and radiotherapy vs. mastectomy) on patients diagnosed with LRR without distant metastasis (DM).

Furthermore, when patients are diagnosed with a LRR, there can be uncertainty as to whether this is a true recurrence (TR) or a new primary (NP) breast cancer. Currently, there is no standardised classification system and therefore, various definitions have been reported in the literature^6^. TR may be defined as cancers with a similar molecular receptor profile (ER; oestrogen receptor / PR; progesterone receptor / HER2) and histological subtype (Ductal/Lobular/ductal carcinoma in situ) when compared to the originally treated cancer. For patients who have had previous BCS, the tumour may be classified as TR if the recurrence location is in the same quadrant of the breast as the original tumour^7^. Patients diagnosed with NP are thought to have a better prognosis when compared to patients diagnosed with a TR^8,9^. However, comparison of tumour morphology, histological subtype, or anatomical location does not enable accurate differentiation between a TR and a NP. Genomic analysis enables a more precise distinction between a TR and a NP^10^. Pan-genomic analysis of paired samples of primary tumour with LRR has been studied in 22 patients with results suggesting its potential clinical utility^11^. However, further studies with larger sample sizes are required.

LRR rates are thought to be declining. A population-based study in the Netherlands^12^ demonstrated that the 5-year local recurrence rate after BCS had fallen from 9.8 to 3.3% (comparison of patients diagnosed between 1988 and 1998 versus 2006–2010). Low 5-year local recurrence rates (<3%) after BCS have also been reported in contemporary trials such as IMPORT-LOW^12^ and FAST-Forward^13^. However, LRR can present in numerous anatomical locations and may occur at any time after the original cancer treatment. A German registry-based study^12^ followed up patients diagnosed with breast cancer between 1999 and 2009 and reported that 10-year cumulative LRR incidence was as high as 8%, however.

In 2012, the UK National Cancer Registration and Analysis Service (NCRAS) and the National Cancer Intelligence Network (NCIN) reported a pilot audit project http://www.ncin.org.uk/view?rid=1043 for patients diagnosed with recurrent and metastatic breast cancer. The pilot involved 15 UK breast units (out of 144) who participated for 6 months in 2011. They identified 137 patients with LRR only and 114 patients with both locoregional and distant recurrences. However, this project did not investigate patient and tumour characteristics or evaluate the patient’s initial cancer treatment. Furthermore, there was a lack of detailed analysis of treatments received by the patients diagnosed with LRR or evaluation of any variation in patient management between participating units. Most importantly, these patients were not followed up to determine survival outcomes.

Currently, there are no UK-specific guidelines for the management of breast cancer LRR. The American National Comprehensive Cancer Network (NCCN) clinical practice guidelines in oncology https://www2.tri-kobe.org/nccn/guideline/breast/english/breast.pdf (BINV-19) provides recommendation as to how patients with LRR should be managed in terms of staging investigations to detect for the presence of DM, type of LRR resection surgery and types of adjuvant treatments to be offered. However, due to the relative lack of high-quality evidence, the guideline acknowledges uncertainties including optimal axillary management, the role of LRR resection in the presence of DM, and which staging investigations should be utilised. A multidisciplinary approach is advocated to optimise patient outcomes. However, to enable tailored treatment recommendations for individual patients and achieve optimal outcome, further research is needed to gather data on tumour characteristics and treatment details of the initial and recurrent cancer.

The number of patients diagnosed with LRR in each UK breast unit per year is relatively small^14^. Therefore, a national collaborative multicentre study is required. Given the concerns about under-reporting of breast cancer LRR to the UK national cancer registries https://www.nabcop.org.uk/content/uploads/2020/07/NABCOP-2020-Annual-Report-V1_high-res.pdf, retrospective analysis using existing routine data source (e.g. Hospital Episode Statistics) is unlikely to provide data on patient management that is reflective of current national practice. Well-established national breast surgery research collaboratives^15–17^ in the UK now have the capacity to generate meaningful prospective datasets that describe current national practice. Therefore, such a national collaborative can be utilised to gather a large prospective cohort of patients diagnosed with LRR with the aim of identifying risk factors for breast cancer LRR, and describe current treatments pathways and patient outcomes.

## Methods and analysis

The aim of the MARECA study is to determine the current management and prognosis of patients diagnosed with breast cancer LRR in the participating UK breast units with the aim of establishing best practice and informing future national guidelines.

The objectives are as follows:Undertake a national survey^14^ of UK breast units in order to establish the current stated practice of breast MDTs regarding the management of patients with breast cancer LRR and identify any potential variation in practice.Establish a prospective cohort of breast cancer patients diagnosed with LRR +/- DM in order to:
Describe current management including:
Use of radiological staging investigations and the proportion of patients found to have DM at presentation.Surgical management including the use of a repeat BCS and sentinel lymph node biopsy.Use of systemic therapies and radiotherapy used to treat LRR.
Investigate risk factors associated with LRR development including those related to the primary breast cancer and its management.
Determine the following oncological outcomes at 3 and 5 years, and evaluate prognostic factors;
Disease free survival (DFS) for patients diagnosed with LRR without associated DM at presentation.Progression free survival (PFS) for patients diagnosed with LRR with associated DM at presentation.Overall survival (OS) for patients diagnosed with LRR with or without associated DM at presentation.
Stratify LRR as a TR or a NP breast cancer using existing clinical classification systems^7–9^ and explore if this distinction affects oncological outcomes.

To determine the feasibility of designing a future translational study. Patients enroled in the study will be invited to provide optional consent for permission to access archival tissue samples of both the primary cancer and the LRR. This would permit comparison of clinical and genomic classification of LRR (TR or NP) against patient survival outcome.

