### Study design

This is a prospective, multicentre cohort study of patients diagnosed with LRR +/- DM with an evaluation of the oncological outcomes of the study cohort at 3 and 5 years. This will be a national research study in collaboration with the Association of Breast Surgery (ABS) Academic and Research committee, the Mammary Fold Academic and Research Collaborative (MFAC) committee and the UK Breast Cancer Trainees Research Collaborative Group (BCTRCG). The study has been adopted on to the National Institute for Health and Care Research (NIHR) clinical research network portfolio enabling research nurses at the participating sites to recruit study participants. The study has also been registered on the NIHR Associate Principal Investigator scheme.

The first phase of the study, the MARECA study national practice questionnaire (NPQ), consisted of scenario-based questions for the breast cancer multidisciplinary teams (MDTs) at the participating centres. The published results^14^ of the NPQ documented the current stated practice of breast cancer LRR management by MDTs, and captured data on practice variations and areas of uncertainty in patient management.

The second phase of the study, the national prospective cohort study, aims to recruit at least 500 women and men newly diagnosed with breast cancer LRR across 50 UK breast units. Recruitment is over a 24 months period. The study has been approved by the London - Brighton & Sussex Research Ethics Committee (21/PR/1128), with the first MREC approval date 07/09/2021 and is a registered clinical trial (ISRCTN11908093). The study recruited its first study participant in January 2022.

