### Study participants

Female or male patients who were previously treated for breast cancer with curative intent and who have recently (within 6 months) been diagnosed with a breast cancer LRR +/- DM. Full inclusion and exclusion criteria are shown in Tables 1 and 2. For the purpose of this study, LRR is defined as a histological diagnosis of invasive breast cancer or ductal carcinoma in situ in the ipsilateral breast (if applicable)/skin/chest wall/regional nodes (axilla/internal mammary/supraclavicular/infraclavicular) following previous breast cancer treatment with curative intent.

**Table 1 T1:** Inclusion criteria.

Inclusion criteria
• Female or male patients more than 18 years old
• Treated for previous unilateral or bilateral breast cancer (invasive cancer including all histological subtypes as well as ductal carcinoma in situ) with curative intent
• No previous evidence of distant metastatic disease
• Recently (within the last 6 months) diagnosed with new ipsilateral breast cancer LRR (biopsy proven invasive cancer including all histological subtypes or ductal carcinoma in situ) +/- distant metastasis
• Able to provide written informed consent
• A minimum of 3 months interval between the resection surgery for the original cancer and the diagnosis of LRR. There will be no maximum interval time period

**Table 2 T2:** Exclusion criteria.

Exclusion criteria
• Patients where the new breast cancer diagnosis is in the contralateral breast
• For patients who present with new bilateral breast cancer, the side with no previous cancer will be excluded
• Patients diagnosed with distant metastatic disease with no evidence of LRR
• Patients diagnosed with angiosarcoma
• Patients with previous history of non-breast cancer treatment that was noncurative in intent
• Patients who have had previous ipsilateral surgery for atypia, benign conditions, or phyllodes tumour and other breast sarcomas AND no previous ipsilateral primary breast cancer resection
• Patients under 18 years old
• Patients lacking capacity to provide written informed consent

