### Study data collection

Data regarding tumour characteristics, investigations performed and treatment details for the patient’s original and recurrent cancer will be collected. Data collection will involve recording patient data that are routinely collected as part of standard clinical practice. Study data will be collected and managed using REDCap^18,19^ (Research Electronic Data Capture) electronic data capture tools The required data fields for the MARECA study prospective cohort study are summarised in the protocol appendices (Supplementary Data File, Supplemental Digital Content 1, http://links.lww.com/JS9/B670).

The collection of oncological outcome data at 3 and 5 years (Fig. 1) post diagnosis will enable the determination of the DFS, PFS and OS of the study cohort. Data collection will include the patient’s survival status, and whether death was related to breast cancer or not, and the date of death. Data on the occurrence of any further LRR or DM, and respective dates will also be collected. To gather these data, the participating units will access their hospital electronic database and hence no direct patient contact is anticipated as part of the study procedure.

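### From this cohort alone, risk factors for developing LRR cannot be estimated: every participant has LRR at entry and the article describes no comparison group

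*Protocol article*

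**What the plan says.** The objectives in Methods and analysis include, among the purposes of the prospective cohort: "Investigate risk factors associated with LRR development including those related to the primary breast cancer and its management". The Background assigns the same purpose to the same patients, proposing to "gather a large prospective cohort of patients diagnosed with LRR with the aim of identifying risk factors for breast cancer LRR".

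The population is fixed elsewhere in the article:
- Study design: "This is a prospective, multicentre cohort study of patients diagnosed with LRR +/- DM".
- Study participants, Table 1, makes the recurrence itself an entry criterion: "Recently (within the last 6 months) diagnosed with new ipsilateral breast cancer LRR".
- Study participants, Table 2, excludes two groups without an ipsilateral LRR: "Patients diagnosed with distant metastatic disease with no evidence of LRR" and "Patients where the new breast cancer diagnosis is in the contralateral breast".
- Study data collection covers enrolled patients only: "Data regarding tumour characteristics, investigations performed and treatment details for the patient’s original and recurrent cancer will be collected".

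Study endpoints lists DFS, PFS and OS, all in patients who already have LRR. Statistical analysis places the two survival time points at 3 and 5 years from the LRR diagnosis and models prognostic factors.

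**The concern.** A risk factor for developing LRR is found by comparing patients who recur with patients who do not, or with the whole treated population from which the recurrences arose. Only patients who recurred are enrolled. The share of them with a given primary-tumour or treatment feature depends on two things at once: how common the feature is among treated patients, and whether it changes the chance of recurrence. The cohort cannot separate the two.

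The article supplies a natural example. Anticipated recruitment and sample size reports that more participants had breast conserving surgery (BCS) for the original cancer than mastectomy. Set beside an objective about risk factors linked to primary management, that imbalance invites interpretation. Yet it could arise entirely because BCS is the more common operation. At stake is an objective that the described data cannot answer, and a possible over-reading of case mix in the report.

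**Working it through.** The article gives no figure for this objective, so there is none to reproduce. The only sample size with a stated basis (165 per group, 2 × 165 = 330) concerns DFS after LRR.

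**1. Does the outcome vary?** Table 1 requires LRR at entry, so 100% of participants have it. With no variation in LRR status, no risk, odds or hazard ratio for its occurrence can be fitted.

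**2. What is missing?** Let pc be the share with a feature among LRR patients (observed) and ps the share among all treated primary breast cancer patients (not collected). Then

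RR = (pc / ps) / [(1 − pc) / (1 − ps)].

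Taking pc = 0.40 as an assumed value:

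| ps (assumed) | Calculation | RR |
|---|---|---|
| 0.20 | (0.40/0.20) / (0.60/0.80) | 2.67 |
| 0.30 | (0.40/0.30) / (0.60/0.70) | 1.56 |
| 0.40 | (0.40/0.40) / (0.60/0.60) | 1.00 |
| 0.50 | (0.40/0.50) / (0.60/0.50) | 0.67 |
| 0.60 | (0.40/0.60) / (0.60/0.40) | 0.44 |

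The same cohort data fit a harmful, neutral or protective feature. A larger sample estimates pc more precisely and says nothing about ps.

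**3. The surgery example.** Assume that 70% of all primaries are treated by BCS and that surgery type has no effect on LRR. Then 70% of LRR patients will have had BCS, a ratio of 0.70/0.30 = 2.33 to 1, with a true relative risk of 1.0.

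**4. Scale of what is unobserved.** The Background quotes a 10-year cumulative LRR incidence of up to 8%. At that figure, 500 LRR patients correspond to about 500/0.08 = 6,250 treated patients, of whom 5,750 have no LRR. For the 684 recruited by 11/12/23, the figures are 684/0.08 = 8,550 and 7,866. This is only an order of magnitude, since the cohort has no upper limit on the interval since the primary cancer.

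**5. Could the wording mean something else?**
- *Prognostic factors after LRR.* The same list of objectives names these separately, for DFS, PFS and OS.
- *Later recurrences.* Study data collection treats these as further LRR, distinct from the LRR that defines entry.
- *Description only.* The Background speaks of identifying risk factors for LRR, which goes beyond description.

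**The case against.** **The endpoints do not depend on this.** Developing LRR is not an endpoint. The sample size and the Kaplan–Meier and Cox analyses serve outcomes after LRR. This stands, and it limits the point to one subsidiary objective.

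**An outside comparator would supply the missing quantity.** The formula needs only the feature's share among all treated primaries. The Background's doubt about registries concerns under-reporting of LRR and fitness for describing management, not the recording of primary cancers. The full protocol, its appendices and the SAP are not shown. This also stands: the claim holds for the cohort used alone, with no comparator described in the article. A reader might infer that the objective could never be met, but the document does not support that.

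**No misuse is planned.** The article uses the excess of BCS patients only to justify continued recruitment, and it proposes no model of time from primary surgery to LRR. That is correct, so the BCS example shows how the objective could be misread and does not criticise a planned analysis.

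**The phrase may be loose wording for description.** The Background faults an earlier audit for not examining tumour characteristics and initial treatment, a gap this cohort can fill. This explains the intent, but two separate statements refer to risk factors for LRR, so the wording still needs correcting.

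**Conclusion.** The point holds in a limited form. As the article describes it, the cohort cannot estimate the relative risk of developing LRR by any primary-tumour or treatment feature, whatever its size. This rests on two facts in the article: LRR is required at entry, and no recurrence-free or external comparison group is described. The numerical shares above are assumptions used to show the range.

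Two stronger readings are not supported. A reader might infer that the main surgery comparison is compromised. It is not: it compares DFS after LRR between two groups of LRR patients, and the secondary PFS and OS endpoints likewise start from patients with LRR. A reader might also infer that spurious risk factors would pass into national guidelines. The Abstract and the stated aim tie guidelines to current management and prognosis, not to causes of LRR.

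This is a correction to one subsidiary objective and does not threaten the study's principal conclusions.

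**What to change.** Reword the objective in Methods and analysis, and the matching Background sentence, to what the cohort can deliver:

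- describe the primary-tumour and treatment characteristics of patients who present with LRR;
- estimate, within the cohort, the association of those characteristics with distant metastasis at presentation, with true-recurrence versus new-primary class, and with DFS, PFS and OS.

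Add a sentence that no inference on the risk of developing LRR will be drawn from the cohort alone.

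If the full protocol or SAP already uses an external comparator of treated primary breast cancers, name it in the objective instead.

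The cost of rewording is one objective, one Background sentence and the matching part of the SAP and report. It needs no new data and no change to recruitment, which was due to close on 31/12/2023.

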### Study endpoints

Primary endpoint:

DFS following LRR resection in patients who present without DM, stratified according to the type of surgery performed for the primary breast cancer (BCS and radiotherapy vs. mastectomy).

Secondary endpoints:PFS in patients who present with LRR with DM.OS in patients with LRR +/- DM at presentation.

